### 6.2.4 Description and justification for the route of administration, dosage, dosage regimen, and treatment period(s)

As longer duration is associated with higher morbidity and mortality (Madzar et al. 2016) SE has to be terminated as quickly as possible. Furthermore recurrence of ictal activity is to avoid. To fulfil the conditions of cessation and stable control one infusion over 10 minutes is planned to generate a high plasma level of an effective drug within a short time. The regimen of one treatment period has also been applied in interventional trials of the past (i.e. Gilad et al. 2008, Treiman et al. 1998, Kapur et al. 2019). The suggested dosages of both trial drugs (VPA 30 mg/kg, LEV 45mg/kg) and the dosage regimen (mg/min) are in accordance to the German guidelines for the treatment of SE in adults (Leitlinien, Deutsche Gesellschaft für Neurologie). In 10 published controlled trials with children and adults of all age groups VPA was administered most often at an initial bolus of 20 or 30mg/kg. Although separate safety studies of the older population are missing the observations of the available studies revealed a good cardiovascular and respiratory tolerability in patients with multiple comorbidities despite high dosages and infusion rates (Sinha and Naritoku 2000, Trinka et al 2014). LEV has shown a favorable tolerability profile in published experiences of over 500 patients who suffered from SE. (Trinka et al 2015) There are no data about SE-treatment in elderly with compromised renal function that would deliver a dosage regimen. In a small retrospective analysis LEV plasma levels measured less than 36 hours after loading and response rate in older people showed no clear benefit of dosages between 20 and 30 mg/kg, so authors suggest a further increasing up to 60mg/kg (Perrenoud et al. 2018). In consideration of the reduced renal elimination on the one hand and the strict demand for efficacy on the other we propose a dosage of 45mg/kg. Frequent controls of renal function and LEV plasma levels beyond the 2 lab controls before and 60 minutes after the intervention are demanded in the clinical setting. With regard to the safety profile of both drugs and the potentially serious or even fatal consequences of SE the ratio of benefit to risk seems clearly in favor of treatment.

## 6.3 Description of the Treatment Procedures

### Visit 1 (V1)

#### Before initiation of intervention

- Setting-up a cardiopulmonary monitoring capable to measure heart rate, oxygen saturation and blood pressure
- **In case of NCSE:** Stop the clinical routine EEG recording before the initiation of intervention and start a new one labeled by the patient ID and WITHOUT further identification data.
- **There must be no delay in the administration of the study drug. The results of the local lab analysis performed at the time of the screening (exception: blood glucose, if unknown) must not be waited for.**

#### During 60 minutes after initiation of intervention

- Monitoring of blood pressure as clinically indicated, heart rate and oxygen saturation continuously during 60 minutes after initiation of infusion. Only parameters requiring emergency treatment (as hypotension, tachyarrhythmia, low oxygen saturation) have to be recorded.
- **In case of NCSE:** It is not possible to replace the EEG device AFTER the start of intervention. The EEG has to be recorded until 60 minutes after the start of intervention

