## 1.3 Risk-Benefit Considerations

Early and effective treatment of SE is associated with lower morbidity and mortality. After the first stage, consisting in the application of benzodiazepines, the choice of medication is uncertain, because sufficient evidence is lacking. If SE cannot be terminated at stage II,

treatment of stage III which requires mechanical ventilation, may constitute an additional risk of its own, especially for older people (Sutter et al. 2014).

According to the published literature (Kapur et al. 2019, Trinkä and Kälviäinen 2017; Trinkä et al. 2015) and the clinical experience VPA and LEV both appear to be safe and effective drugs in the treatment of SE. In the past, VPA was administered in effective doses from 15 to 45 mg/kg. Safety studies showed a generally low incidence of side effects (<10%; mainly thrombocytopenia and mild hypotension), that occurred independently of infusion rates. The most severe side-effects are hepatotoxicity and also encephalopathy, which has been observed to rarely follow hepatic dysfunction or hyperammonaemia (Trinkä et al. 2014). LEV displays a low risk of side effects and drug interactions. Side effects included psychiatric disturbances, somnolence, fatigue and headache. The safety profile of the liquid formulation was comparable to the oral formulation. In single cases, thrombocytopenia, agitation, delirium and psychosis were described (Beuchat et al. 2018; Hwang et al. 2014).

Considering the lack of sufficient and robust scientific evidence, the life-threatening nature of the condition and the known poor outcome of older patients suffering from SE the conduction of this trial appears to be both needed and justified.

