### 5.5.2 Dealing with Side-effects

To ensure the appropriate recognition and treatment of complications during the intervention this chapter focusses on possible side-effects of the **i.v.application** of VPA or LEV.

In safety studies the following side-effects of **VPA** have been reported:

- Transient: dizziness, headache, somnolence, taste perversion, nausea, vomiting, injection-site reactions (Devinsky et al. 1995)
- Transient hypotension (Ramsay et al. 2003)
- Asymptomatic hyperammonaemia (DeWolfe et al. 2009)
- Respiratory depression (Trinka et al. 2014)
- Hepatic abnormalities (Trinka et al. 2014)

Case reports also described encephalopathy with or without concomitant hyperammonaemia, acute hepatic failure and acute pancreatitis (reviewed in Trinka et al. 2014).

According to the review (Trinka et al. 2014) about experiences with cumulative 860 patients suffering from various types of SE and treated with i.v. VPA dizziness, thrombocytopenia and mild hypotension are the reported most common side-effects. With regard to the prescribing information (Fachinformation Orfiril® Desitin) the following possible side-effects should also be considered:

- metabolic acidosis, renal failure (frequency unknown)
- Leukopenia, elevation of liver enzymes (often, 1 to 10 of 100 treated subjects)
- Tremor, confusional state (often)
- Bleedings, severe hepatic damage (occasional, 1 to 10 of 1000 treated subjects)
- Severe pancreatic damage (rarely, 1 to 10 of 10.000 treated subjects)

In retrospective case series and safety studies on over 1000 patients including more than 500 patients with SE so far **LEV** has most often been associated with somnolence and sedation (Trinka et al. 2015). In single cases LEV has been associated with delirium (Hwang et al. 2014; Kumar et al. 2014; Foley and Bugg 2010).

Also the following possible side-effects have been reported (Fachinformation Levetiracetam UCB®):

- nasopharyngitis, headache, dizziness (very often, 1 or more of 10 treated subjects)
- agitation, anxiety, hostility, insomnia, depression (often, 1 to 10 of 100 treated subjects)
- nausea and vomiting (often)
- suicidal ideation (occasional)
- thrombocytopenia, leukopenia (occasional)
- cognitive impairment (occasional)
- pancreatitis, severe hepatic or renal damage, encephalopathy (rarely)

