The ESET trial (Kapur et al 2019) reports a depressed level of consciousness and respiratory distress as most frequent serious adverse events. The incidence of these events did not differ significantly between the treatment groups (LEV, VPA and fosphenytoin). Numerically depression of consciousness (15 vs. 9) and respiratory depression (10 vs. 8) was more often in the LEV treatment arm than in the VPA treatment arm (Supplement to Kapur et al. 2019).

During the intervention of ToSEE the relevant acute side-effects as hypotension and respiratory depression are recorded by the cardiopulmonary monitoring. In addition at least one member of the trial staff will guard the patient and check his clinical status repeatedly during 60 minutes after the start of the intervention. According to the clinical standard of SE-treatment rescue medication and airway-management shall be provided. The lab analysis before the intervention and after the observation period serves the detection of pre-existent and acute hepatic or renal impairment.

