#### 7.1.3 Documentation and Reporting

Adverse events (AE) will be documented for patients in both treatment arms (VPA and LEV) **from the moment of initiating the infusion of IMPs until the end of the study.**

AE reports comprise any newly reported events as well as worsening of pre-existing conditions (i.e. increased intensity/grading) during the predefined reporting period of events.

AEs are documented on specified AE forms provided in the CRF.

If an AE fulfils any of the criteria for an SAE (see chapter 7.4 for SAE-definition), both the AE pages of the CRF **and** the SAE form must be completed. This applies to all SAEs, **whether or not they are considered to be related to trial treatment.**

For both serious and non-serious AEs, documentation should be supported by an entry in the patient's health record. Required information in the patient's health record should include:

- type of AE
- grade/severity/intensity acc. to e.g. NCI CTCAE 5.0
- seriousness (see also section 7.4)
- onset date

- end date
- actions required
- outcome
- assessment of its relationship to trial drug

All abnormal physical and/or laboratory results which are considered to be clinically relevant by the investigator should be recorded as AEs. If an abnormal laboratory result meets any of the criteria for a SAE, this must also be reported on the SAE Form.

Adverse Events are classified by their seriousness, intensity/severity and relationship to the IMP (see also 16.1).

The following events could be SE-related clinical outcomes/endpoints. Occurrence will be documented as (S)AEs and furthermore within the CRF in addition and independently from the (S)AE-form:

- Indication for the need of an emergency medication (different from allocated study drug) during 60 minutes after initiation of infusion
- Respiratory depression requiring noninvasive/invasive ventilation (oxygen supply excluded) during 60 minutes after initiation of infusion
- SE-recurrence/seizures after successful intervention
- SE- associated ventilation until hospital discharge
- Delirium
- Infections treated with i.v. anti-infectives (type of infection)
- Other complications: sedation, dizziness nausea, vomiting, new thrombocytopenia, leukopenia, new elevation of liver enzymes, acute new liver failure or pancreatic damage, hyperammonaemia, tremor, psychiatric complications.

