#### Safety

- Mortality
- Need for any emergency medication (different from allocated study drug) during 60 minutes after initiation of study intervention
- Need for ventilation (noninvasive/ invasive) during 60 minutes after initiation of intervention
- ~~Number of patients with SE-associated ventilation until hospital discharge~~
- Intrahospital complications
  - Incidence of delirium as diagnosed by the treating physician
  - Infections requiring intravenous administration of anti-infectives
  - Adverse events related to infusion/subsequent therapy with antiepileptic drug (sedation, dizziness, nausea, vomiting, thrombocytopenia, leukopenia, hypotension, new elevation of liver enzymes, hyperammonaemia, acute new liver failure or pancreatic damage, tremor, psychiatric abnormalities)

The mRS is the recommended outcome measure in stroke trials as it is directly relevant to the patient's ability to return to daily life. Its scores range from 0 (no impairment) to 6 (death) and include special items as walking and independence that are indicative of the degree to which a patient is competent to participate in daily activities (Lees et al. 2012). As most of the seizures occurring in elder people are caused by an underlying structural brain injury the clinical phenomenology of focal convulsive SE or nonconvulsive SE may imitate stroke-related deficits. Thus, the effects on functional outcome may be quantified meaningfully and appropriately by the mRS. The Barthel Index is also a well-established clinicometric scale which is utilized to reflect elderly patient's need for care in particular and includes basic activities such as transfer and personal hygiene (Mahoney and Barthel 1965).

The secondary endpoints will provide valuable insights into the disorder in this age group. There is a special emphasis on characteristics of SE and concomitant intrahospital complications to provide an equal evaluation of the efficacy and safety of antiepileptic treatment in the elderly.

The combination and comparison of the retrospective and prospective assessment of mRS and BI are chosen in order to quantify its consequences on functional outcome.

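### Hypotension is a safety endpoint, but below the level of emergency treatment the protocol leaves its capture to discretionary adverse-event reporting, so it is likely undercounted and may be reported unevenly between arms

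*Protocol*

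**What the plan says.** **Endpoint.** Protocol 8.2.2 (Safety) lists, among adverse events related to the infusion or later therapy, "sedation, dizziness, nausea, vomiting, thrombocytopenia, leukopenia, hypotension, new elevation of liver enzymes" and further items. No severity or treatment condition is attached to hypotension.

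**Expectation.** Section 1.3 describes the side effects of VPA as "<10%; mainly thrombocytopenia and mild hypotension". Section 5.5.2 lists transient hypotension for VPA and, after dizziness, says that "thrombocytopenia and mild hypotension are the reported most common side-effects". Its list for levetiracetam (LEV) does not include hypotension.

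**Recording.** Section 5.5.2 says that during the intervention "the relevant acute side-effects as hypotension and respiratory depression are recorded by the cardiopulmonary monitoring". The instruction to sites in 6.3 is narrower: "Monitoring of blood pressure as clinically indicated, heart rate and oxygen saturation continuously during 60 minutes after initiation of infusion", followed by "Only parameters requiring emergency treatment (as hypotension, tachyarrhythmia, low oxygen saturation) have to be recorded".

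**CRF list.** Section 7.1.3 lists possible endpoint events to be documented as (S)AEs and also in the CRF separately from the (S)AE form. Its last item begins "Other complications: sedation, dizziness nausea, vomiting, new thrombocytopenia, leukopenia, new elevation of liver enzymes" and goes on to liver failure, pancreatic damage, hyperammonaemia, tremor and psychiatric complications. Hypotension is not in it.

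**Unblinding.** Treatment is unblinded from 15 minutes in failures and by 60 minutes at the latest in everyone (6.3, 8.1.1).

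**The concern.** The endpoint counts hypotension of any degree, while the recording duty in 6.3 covers only what needs emergency treatment. The mild, transient fall that the protocol expects under VPA lies outside that duty. It can still be reported as an AE, but this depends on whether a reading was taken and whether the investigator thought it relevant.

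Two effects follow. The first is undercounting in both arms, which shrinks any true difference. The second is uneven reporting. The drug is known within the hour, hypotension is named for VPA and not for LEV, and a note under Visit 2 in 6.3 directs attention to unexplained hypotension specifically during VPA treatment. This sits badly with the statement in 8.1.1 that the secondary parameters are not open to biased evaluation.

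Safety bears on the trial's conclusion: 1.2.1 says that superior efficacy of one drug may be offset by a better safety profile of the other. Section 6.2.4 adds that separate safety studies of VPA in older people are missing.

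**Working it through.** The point concerns data capture, so the main check is a comparison of sections.

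1. *What counts?* Hypotension, no threshold (8.2.2).
2. *Is it measured?* A monitor able to measure blood pressure is attached (6.3, before the intervention), blood pressure is among the screening vital signs (6.2.1), and cardiopulmonary monitoring runs to 60 minutes (7.2 and the schedule). Within those 60 minutes, 6.3 makes heart rate and saturation continuous but fixes no blood-pressure readings.
3. *Must the value be recorded?* 5.5.2: yes, by the monitoring. 6.3: only if emergency treatment is required. These differ.
4. *Is there a dedicated CRF entry?* Not according to 7.1.3. The Visit 2 data list in 6.3 has no hypotension item either.
5. *What remains?* The AE form. An AE includes any unfavourable sign (7.1.1), abnormal physical findings are recorded if the investigator considers them clinically relevant (7.1.3), and the mild grade covers events needing no intervention (16.1.2). This route is open but discretionary.
6. *Is the reporter blind?* Not after 60 minutes. The eCRF is provided after registration in the database, which may take up to 24 hours on a working day (6.2.2), so AE entry can follow unblinding.

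**Scale, by illustration only.** The protocol gives no rate for hypotension and no capture share. The one figure borrowed is 454 evaluable patients (8.4). It reproduces with unpooled variance: (1.960 + 0.842)² × (0.60×0.40 + 0.47×0.53) / 0.13² = 227.15 per arm, or 454 in total after rounding down.

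Assume 227 per arm, a true rate of 10% under VPA, 5% or 3% under LEV, and the same captured share *c* in both arms. Expected count = 227 × rate × *c*. Power of a two-sided 5% comparison = Φ[(d − 1.960·SE₀)/SE₁], with SE₀ from the pooled and SE₁ from the separate variances. For 10% v 5% and *c* = 1: SE₀ = √(2×0.075×0.925/227) = 0.02472, SE₁ = √((0.10×0.90 + 0.05×0.95)/227) = 0.02461, and (0.05 − 0.04846)/0.02461 = 0.063, so power is 0.53.

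| Captured share *c* | 10% v 5%: counts | Difference (points) | Power | 10% v 3%: counts | Power |
|---|---|---|---|---|---|
| 1 | 22.7 v 11.4 | 5.0 | 0.53 | 22.7 v 6.8 | 0.86 |
| 0.5 | 11.4 v 5.7 | 2.5 | 0.29 | 11.4 v 3.4 | 0.56 |
| 0.25 | 5.7 v 2.8 | 1.25 | 0.16 | 5.7 v 1.7 | 0.31 |
| 0.1 | 2.3 v 1.1 | 0.5 | 0.09 | 2.3 v 0.7 | 0.15 |

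The normal approximation is rough in the last row, where counts are very small.

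Uneven capture can also create a difference. With a true rate of 10% in both arms, capture of 0.5 under VPA and 0.25 under LEV gives 227×0.10×0.5 = 11.4 v 227×0.10×0.25 = 5.7 events.

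**The case against.** The strongest reply is that AE reporting, and not the monitoring rule in 6.3, is the data source for this endpoint. Section 8.2.2 frames the item as adverse events. AEs are collected from the start of infusion, their definition has no treatment threshold, and the mild grade covers events needing no intervention. Nothing in 6.3 limits chapter 7. This stands. A reader might infer from 6.3 that mild hypotension goes uncounted, or that the arms are compared on treated hypotension only. The documents do not support either reading.

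Other points carry some weight:

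- A monitor is attached and a staff member checks the patient repeatedly for 60 minutes (5.5.2), so many readings will probably exist. Whether they are entered is another matter.
- The parenthesis in 6.3 could be read as naming hypotension as something to record. If so, the sentence has two readings, and sites may differ in which they follow.
- Omission from the 7.1.3 list removes only the additional CRF entry; the event stays reportable as an AE. But that entry is the one that does not depend on AE judgement.
- The working instructions mentioned in 8.1.1 cover the first 60 minutes and AE reporting. They are not part of the protocol text and may say more.
- A numerical definition can be left to the SAP, and its absence is not criticised here. An SAP cannot, however, recover values that were never entered.

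**Conclusion.** The concern holds as a defect of data capture. Sections 5.5.2, 6.3, 7.1.3 and 8.2.2 do not agree on how hypotension enters the data. Below the level of emergency treatment it depends on discretionary AE reporting without fixed readings, by staff who may know the drug. Undercounting is likely and uneven reporting is possible.

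The size cannot be derived. The ceiling of 10% in 1.3 applies to VPA side effects as a whole, so using it for hypotension alone is an upper-end assumption. The LEV rates and captured shares above are also assumed. A reader might conclude that half to nine tenths of the endpoint is lost by rule. That figure is only one minus an assumed captured share of 0.5 or 0.1, with AE reporting taken to add nothing. Nor is mild hypotension named as the single most common side effect: it is one of three, for VPA.

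The consequence is limited to one component of a secondary safety endpoint whose analysis 8.4 calls mainly explorative. The primary analysis is unaffected. It is still worth correcting, because the protocol intends to weigh safety against efficacy.

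**What to change.** Reconcile 5.5.2, 6.3, 7.1.3 and 8.2.2:

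- Add hypotension to the 7.1.3 list of events documented in the CRF independently of the (S)AE form. This also covers hypotension after the first hour.
- Enter in the eCRF the blood-pressure values available from the monitor already attached, for example at screening, T15, T30 and T60, plus the lowest value up to T60, with a field for whether it was treated. Enter values whether or not treatment followed, and mark a missing value as not taken, so that the number of patients with readings can be reported by arm.
- Derive the endpoint with one definition for both arms, for example a CTCAE 5.0 grade, which is already the protocol's severity scale. The detail can go in the SAP.

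Cost: about six eCRF fields (four readings, the lowest value, the treated flag) and a little data entry. Blood pressure is already assessed at screening, a staff member is already present for the hour, and the Glasgow Coma Scale is already taken at T15, T30 and T60. The change concerns data recording only and sets no monitoring or treatment rule.

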## **T0 - Initiation of intervention**

Details to the administration of study drugs – see 0

- Note the time of initiation
- Check for the availability of the unblinding envelope

## **T15 – 15 minutes after initiation of intervention**

- Check for cessation of convulsive seizures or minimal rhythmic motor activity or cessation of EEG signs of NCSE according to Salzburg criteria (Leitinger et al. 2016)
  - Cessation of EEG signs of NCSE defined as:
    - No rhythmic epileptiform discharges that are continuously present for at least 10 seconds
    - No rhythmic delta/theta activity **or** rhythmic delta/theta activity  $\leq 0.5$  Hz that is continuously present for at least 10 seconds
- Administer GCS

## **T30 – 30 minutes after initiation of intervention (+/- 5 minutes)**

- Administer GCS

## **T60 – 60 minutes after initiation of intervention (+/- 5 minutes)**

- Administer the GCS and perform brief neurological exam: orientation, horizontal extraocular movements, motor drift of both arms and legs, sensation, language
- Obtain a blood sample (EDTA and heparine-plasma and/or serum) for the following parameters:
  - blood count
  - alanine aminotransferase, aspartate aminotransferase, gamma-glutamyl-transferase
  - creatinine, blood urea, glomerular filtration rate
  - sodium
  - level of valproate, level of levetiracetam

## **During 45 minutes after T15 - until T60**

- Check for the recurrence of convulsive seizures or minimal rhythmic motor activity or recurrence of EEG signs of NCSE according to Salzburg criteria
- Unblind the medication in case of recurrence of ictal activity (envelope), the subsequent procedure is to be executed in accreditation of the treating physician (as watch and wait/ repetition of infusion with the same antiepileptic drug/ further treatment with another antiepileptic drug)
- Note the time of unblinding (how many minutes after T0? – must be  $\geq 15$  min )

